## Abstract

**Methods::**

This is a single-center, phase II clinical trial to evaluate the efficacy and safety of Efavirenz in addition to standard of care in patients diagnosed with adult or late juvenile-onset NPC with cognitive impairment. All enrolled patients will be treated orally with 25 mg/d of Efavirenz for 52 weeks (1 year). Secondary objectives include evaluating clinical (neurological and neuropsychological questionnaires) and biological (imaging and biochemical biomarkers) parameters.

**Discussion::**

NPC is still an unmet medical need. Although different therapeutic approaches are under study, this is the first clinical trial (to the best of our knowledge) studying the effects of Efavirenz in adult- and late-juvenile-onset NPC. Despite the small sample size and the single-arm design, we expect the results to show Efavirenz’s capacity of activating the CYP46 enzyme to compensate for NPC1 deficiency and correct synaptic changes, therefore compensating cognitive and psychiatric changes in these patients. This study may provide direct benefit to enrolled patients in terms of slowing down the disease progression.

## 1. Introduction

### 1.1. Background and rationale

Niemann-Pick disease Type C (NPC) is a genetic, neurodegenerative disorder with a life expectancy ranging between 1 – and 30 years after diagnosis. From a clinical perspective, NPC usually affects the viscera (splenomegaly and/or hepatomegaly), but it is, above all, a neurological disease. It is a progressive disease without curative treatment and with only 1 treatment approved to date – with limited efficacy (Miglustat, Zavesca®). In 2019, adult-onset NPC prevalence in Spain was 27 patients, of which ten are being treated at Bellvitge University Hospital (BUH).

The disease is classified according to the age of onset of the neurological symptoms in: early infantile (before 2 years of age); late infantile (between 3 and 5 years of age); early juvenile (between 5 and 14 years of age); late juvenile (between 14 and 16 years of age); and adult (from 16 years of age onwards).

The clinical presentation includes psychomotor development regression, epilepsy, ataxia, vertical supranuclear ophthalmoplegia, bulbar syndrome, dystonia, splenomegaly, cognitive impairment, behavioral disorders, and symptoms of psychiatric disorders, with behavioral/cognitive symptoms being most common in adults. Altogether, these symptoms point towards synaptic changes as a key element in disease development, similar to other dementias (e.g., Alzheimer’s), where cognitive impairment correlates with the loss of synapses.

In 95% of the cases, genetic mutations in the NPC1 protein are responsible for disease development. The NPC1 protein is involved in the intracellular transport of cholesterol.^[1–3]^ From a cellular and molecular perspective, one of the main hallmarks of NPC is the accumulation of cholesterol and sphingolipids in lysosomal compartments, where NPC1 is found.^[4]^ Although lipid accumulation occurs in all cell types, neurons are especially vulnerable to NPC1 deficiency, suggesting that neuronal function is especially related to this protein. Also, NPC1 is found not only in cell bodies, where endosomes and lysosomes are highly abundant,^[5]^ but also in axon terminals and synaptosomes,^[6,7]^ pointing towards a synaptic role from NPC1 other than participating in the lysosomal degradation pathway.

Some authors demonstrated the importance of cholesterol synaptic redistribution and elimination for the correct development of long-term potentiation (LTP).^[8]^ LTP is a major event for synaptic plasticity, involved in processes like memory, learning, and emotional responses. Cholesterol loss during LTP has been associated with the enzyme CYP46A1, mobilized to the plasmatic membrane in response to synaptic stimulation, hydroxylating cholesterol, making it more soluble, and mediating the main pathway for its degradation in the brain.^[9,10]^

Given that NPC1 can bind cholesterol and participate in intracellular cargo mobilization, we hypothesized that NPC1 would have a synapse-specific role in redistributing cholesterol and mobilizing the CYP46A1 enzyme to the synaptic membrane, required for LTP. We believe that the pharmacological activation of CYP46A1 could compensate for NPC1 deficiency and correct synaptic changes, therefore compensating cognitive and psychiatric alterations in patients with NPC.

Preclinical data on Npc^nmf164^ mice^[11]^ (which have the D1005G mutation in the NPC1 gene and develop NPC slower than NPC1^−/−^ mice) have provided evidence that low-dose Efavirenz (EFV) (compared to the dosages used with antiretrovirals) modifies the morphological, molecular, and functional changes in their synapses.^[12]^ It also improved cognitive and psychiatric changes, reverted synaptic defects through pharmacological activation of the enzyme CYP46, and increased the life expectancy of Npc^nmf164^ mice by 30%.^[12]^ These encouraging results are the rationale for conducting this clinical trial on this orphan disease.

According to the summary of product characteristics (SmPC), EFV was authorized in May 1999 as a non-nucleoside reverse transcriptase antiretroviral inhibitor and, currently, it is a generic drug used in the combined antiviral treatment of human immunodeficiency virus-1^[13]^ in infected adults, adolescents and children aged 3 months and older that weigh at least 3.5 kg. In adults, the recommended oral dose of EFV combined with nucleoside reverse transcriptase inhibitors with or without a protease inhibitor is 600 mg once a day (600 mg/d). It is a treatment administered “for life” in patients infected with HIV.

This clinical trial aims to evaluate the efficacy and safety of EFV at an oral dose of 25 mg/d in patients diagnosed with adult or late juvenile-onset NPC with cognitive impairment.

### 1.2. Explanation for the choice of comparators

Given the clinical trial characteristics, all patients included in the clinical trial will be treated orally with 25 mg/d of EFV for 52 weeks (1 year), in addition to Standard of Care (SoC).

### 1.3. Objectives

The primary, secondary, and safety objectives are summarized in Table 1.

**Table 1 T1:** Summarized study objectives.

Primary Objective	
•To evaluate the efficacy* and safety of EFV at an oral dose of 25 mg/d, in addition to standard treatment, in patients diagnosed with adult or late juvenile-onset NPC with cognitive impairment.	
*Note: Given that adult or late juvenile-onset NPC is rare and causes progressive cognitive impairment, treatment with EFV will be considered effective if it “slows down or stops cognitive impairment in patients diagnosed with adult or late juvenile-onset NPC with cognitive impairment.” Meaning, it is hoped that after 1 year of treatment, these patients remain at the baseline with respect to cognitive impairment.	
Secondary objectives	
**Clinical**	• Neurological: To evaluate the change in the following questionnaires/scales:
	SARA
	EAT-10 score.
	PDS
	• Neuropsychological (protocol used in clinical practice): To evaluate the change in the following questionnaires/scales:
	CDR-SoB
	Verbal memory: FCSRT
	a-BT
	Verbal fluency: Semantic and phonetic cues
	TMT A and B
	STROOP
	WAIS and the block design, symbol search and vocabulary subtests (WAIS-III/WAIS-IV)
	BNT, and the Naming and Semantic Knowledge subtests
	JLO
	DEX
	NPI
	AES
	BDI
	C-SSRS
**Biological**	• To evaluate the change in functional and imaging biomarkers related to NPC:
	^18^FDG PET—scan
	Brain MRI
	Abdominal ultrasound
	Oculography
	• Evaluate the change in biochemical biomarkers related to NPC:
	Oxysterols
	Lyso-SM-509
	24-OH-Cholesterol
	Beta-Amyloid, Tau, and phosphorylated Tau
**Safety**	• To evaluate the safety of EFV in patients diagnosed with adult or late juvenile-onset NPC with cognitive impairment.

18 FDG PET—scan = ^18^Fluorodeoxyglucose Positron emission tomography scan, a-BT = abbreviated Barcelona test, AES = apathy evaluation scale, BDI = Beck’s depression inventory, BNT = Boston naming test, CDR-SoB = clinical dementia rating scale-sum of boxes, C-SSRS = Columbia suicide severity rating scale, DEX = dysexecutive questionnaire, EAT-10 = the eating assessment tool score, EFV = efavirenz, FCSRT = free and cued selective reminding test, JLO = judgement of line orientation test, MRI = magnetic resonance imaging, NPC = Niemann-Pick disease type C, NPI = neuropsychiatric inventory, PDS = Pineda disability scale, SARA = scale for the assessment and rating of ataxia, STROOP = stroop color and word test, TMT = trail making test, WAIS = Wechsler adult intelligence scale.

### 1.4. Trial design

This is a single-center, phase II clinical trial to evaluate the efficacy and safety of EFV, in addition to SoC, in patients diagnosed with adult or late juvenile-onset NPC with cognitive impairment.

All enrolled patients will be treated orally with 25 mg/d of EFV for 52 weeks (1 year), in addition to SoC. According to the SmPC, the recommended dose of EFV as an antiretroviral for adults is 600 mg/d orally.

## 2. Methods: Participants, interventions, and outcomes

### 2.1. Study setting

This is a single-center clinical trial. Therefore, this study will be carried out at BUH (L’Hospitalet de Llobregat, Barcelona, Spain) and will be coordinated by the Neurology Department. This is a fully equipped tertiary hospital.

### 2.2. Eligibility criteria

Patients that are to be enrolled in the trial must meet all the inclusion criteria and none of the exclusion criteria.

#### 2.2.1. Inclusion criteria.

Patients must:

•Be at least 14 years of age, of both genders.•Be diagnosed with adult-onset NPC based on a genetic study with 2 genetic mutations related to this disorder OR 1 genetic change, 1 positive filipin stain, and a positive biomarker.•Have mild to moderate cognitive impairment with a global Clinical Dementia Rating (CDR) score of 0.5 to 2 and/or a CDR-SoB ≤ 12.•Have the capacity (at the investigator’s discretion) to understand the nature and risks of the trial and the relevant information given, the capacity to decide whether to participate, and sign the written informed consent.•Have a live-in caregiver available more than 5 days a week that can inform the patient’s medical situation, understand the nature and risks of the trial, and sign the written informed consent.•Be proficient in Spanish (the language in which cognitive tests will be conducted).•Have sufficient visual and auditory acuity for understanding explanations given and neuropsychological tests.•Have a minimum 8 years of schooling.•Be on Miglustat treatment (only treatment indicated for NPC) with a stable dose for the last 3 months.•In the case of women of child-bearing potential (i.e., the period between menarche and menopause), have a negative pregnancy test.•In the case of women of child-bearing potential, commit to use highly effective contraceptive measures, which include barrier methods in combination with other contraceptive measures (e.g., oral, or other hormonal contraceptives) or commit to sexual abstinence until at least 12 weeks after the final dose of EFV.•In the case of male patients, commit to use barrier contraceptives (condoms) until at least 12 weeks after the final dose of EFV.•Sign the written informed consent.

***Note***: Although the primary target population of the study is patients with adult-onset NPC (i.e., patients > 16 years old), we will also enroll patients aged between 14 and 16 years old (patients with late juvenile-onset NPC). The justification for including the late juvenile population (between 14 and 16 years old) in the study is that NPC also causes cognitive impairment in this age interval.

#### 2.2.2. Exclusion criteria.

•Any sign or suspicion of a diagnosis other than NPC.•Active Central Nervous System infections that may interfere with normal brain function.•History of severe traumatic head injury.•History of severe psychiatric illnesses: bipolar disorder, schizophrenia, major depressive disorder.•Risk of suicide, according to the live-in caregiver or investigator.•History of substance abuse or dependence.•Presence of cerebrovascular disease that can explain the cognitive impairment (in the investigator’s opinion).•Inability to tolerate the study-related procedures.•Stage IV chronic kidney disease.•Chronic liver disease or increased Aspartate Aminotransferase or Alanine Aminotransferase levels (≥3 times the upper limits of normal).•Chronic viral hepatitis B or C.•Patients with systemic immunosuppression.•Unstable epilepsy (at the investigator’s discretion) in the last 3 months*.

***Note:** Those with controlled/stable epilepsy can be enrolled.

•History of malignancies not considered stable or cured (in general, patients who have not been treatment-free for at least 5 years before screening and considered to be at low risk of recurrence by the treating physician).•Severe dementia that hinders the completion of cognitive tests and evaluations.•History of allergy/hypersensitivity to EFV or to any of the excipients found in the formula.•Patients using anticoagulants are not excluded from the trial but will NOT be offered the possibility to join the lumbar puncture group.•Concomitant treatment with any of the following: terfenadine, astemizole, cisapride, midazolam, triazolam, pimozide, bepridil, or ergot alkaloids (e.g., ergotamine, dihydroergotamine, ergonovine, and methylergonovine)*.

****Note*:** These drugs are substrates of the CYP3A4 that could cause a competitive inhibition of the EFV metabolism and generate serious and/or life-threatening AEs (e.g., cardiac arrhythmias, prolonged sedation, respiratory depression).

•Co-administration with elbasvir and grazoprevir due to the potential of EFV to significantly decrease plasma concentrations of both drugs.•Use of herbal medicinal products containing St. John’s Wort (*Hypericum perforatum*) due to the risk of decreasing the plasma concentrations and the clinical effects of EFV.•Family history of sudden death or congenital prolongation of the QTc interval or any other clinical condition known to prolong the QTc interval.•Family history of symptomatic cardiac arrhythmias, clinically relevant bradycardia, or congestive heart failure associated with a reduced left ventricular ejection fraction.•Severe disturbances of electrolyte balance, such as hypokalemia or hypomagnesemia.•Concomitant treatment with drugs known to prolong the QTc interval, such as class IA and class III antiarrhythmics; neuroleptics; antidepressant drugs; certain antibiotics (i.e., macrolides, fluoroquinolones); imidazole and triazole antifungal agents; certain non-sedating antihistamines (i.e., terfenadine, astemizole); cisapride; flecainide; certain antimalarials; and methadone.

### 2.3. Interventions

The study intervention is EFV. All patients will be treated orally with 25 mg/d of EFV for 52 weeks (1 year), in addition to SoC. Despite this established 25 mg/d dose, successive blood analyses will be performed during the trial, and those patients with no evidence of a blood 24-OH-Cholesterol increase ≥ 1.5 times their baseline levels will have their EFV dose increased up to 200 mg/d.

According to the SmPC, the recommended antiretroviral dose of EFV for adults is 600 mg/d PO, combined with nucleoside reverse transcriptase antiretroviral inhibitor with or without a protease inhibitor. The dose selected for this trial (25 mg/d) is the 1 administered to the pediatric population with 3.5 to <5 kg of weight. Also, as recommended by the SmPC, patients will be advised to take the medication at bedtime.

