#### 2.3.1. Rationale for dose selection.

Preclinical studies using NPC mouse models used an Efavirenz dose 300 times smaller than the 1 used in HIV patients.^[14]^ Although very small, the dose used has been proven to activate CYP46 and efficiently promoted the recycling of cholesterol in the brains of normal mice.^[14]^

However, extrapolating preclinical doses to a clinical setting is challenging. The significant differences in body size, brain size, and the blood-brain barrier must be considered, among other things. Also, administering humans with a dose as low as the 1 administered in mice would risk not having the desired effect.

Notably, 1 clinical trial (NCT03706885, ClinicalTrials.gov) is currently being conducted in patients with Alzheimer’s dementia using oral doses of EFV of 50 and 200 mg/d to activate CYP46 in the brain.

In light of all that, the study team has selected a dose of 25 mg/d of EFV, considering that the desired effect should be observed with this dose – a dose 24 times smaller than the recommended antiretroviral dose for HIV patients (600 mg/d). Given that increases in plasma 24-OH-Cholesterol concentrations (≥1.5 times the pre-EFV baseline values) have been observed in the preclinical studies, we will perform successive blood tests (every 3 months). If no 24-OH-Cholesterol increases ≥ 1.5 times the pre-EFV baseline values are observed, we shall consider increasing the dose to up to 200 mg/d.

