### 2.7. Outcomes:

Primary and secondary outcomes are summarized in Table 2.

**Table 2 T2:** Summarized outcome measures.

Primary outcome measure	
Change (not deterioration) in cognitive performance at 52 wks of starting treatment with EFV, assessed by:	
CDR-SoB score.	
FCSRT score (to evaluate verbal memory).	
The executive functions as per the following:	
a)a-BT scores in the digit span subtest.	
b)a-BT scores in the mental control subtest.	
c)Scores in verbal fluency subtest: semantic and phonemic tasks.	
d)TMT A and B scores	
e)SCWT scores.	
Secondary outcome measures	
**Clinical**	Neurological: Changes at 52 wks of starting treatment with EFV relative to baseline in:
	SARA score
	EAT-10 score.
	PDS score
	• Neuropsychological (protocol used in clinical practice): In general, the scaled score will be determined for the following questionnaires/scales:
	CDR-SoB^*^ score.
	*Note: It offers a specific score from 0 to 18, the higher the score the greater the severity.
	FCSRT score
	a-BT assessment in the following domains:
	◦Orientation, digit span, automatized sequences (e.g., counting to 20, d of the wk, mo of the yr), comprehension of verbal commands, and comprehension of complex verbal material (i.e., yes-or-no answers to BDAE-based questions) subtests’ scores.
	◦Bilateral gesture-based limb praxis test
	◦Visual memory (i.e., figures)
	◦Reading, repeating, and writing
	◦Mental and written arithmetic
	◦Reciprocal coordination
	◦Unilateral alternating sequences subtest (e.g., serial hand tests, such as fist-palm-side, tapping).
	◦Constructional praxis (drawing copy).
	Verbal Fluency score: Semantic and phonemic tasks
	TMT A and B scores
	SCWT score
	WAIS-III/WAIS IV
	BNT, Naming and Semantic Knowledge subtests’ scores
	JLO Test score.
	DEX questionnaire score.
	NPI score.
	AES score.
	BDI score.
	C-SSRS score.
**Biological**	• Brain ^18^FDG PET–Scan: Quantification of cerebellar, cortical, and thalamic metabolism.
	• Brain MRI: Cortical, white matter, basal ganglia, and cerebellar structures volumetric analysis.
	• Abdominal ultrasound: Spleen size (cm).
	• Oculography: initial speed, amplitude, and execution speed of vertical and horizontal saccades
	• Plasma Oxysterols levels
	• Plasma Lyso-SM-509 level
	• Plasma 24-OH-Cholesterol level
	• Cerebrospinal Fluid (CSF) Beta-Amyloid, Tau, and phosphorylated Tau levels
**Safety**	• Number of adverse events (AEs) according to seriousness, severity, and relationship with EFV.

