#### 2.7.1. Study procedure.

Study candidates will be screened during visit 1. Those who meet all the inclusion criteria and none of the exclusion criteria will be invited to participate. Both patient and caregiver must sign the written informed consent, a sine qua non condition for enrollment. Seven study visits will be performed for enrolled patients, and all the information detailed in Table 3 will be gathered.

**Table 3 T3:** Participant timeline.

	Visit 1 (baseline visit)	Visit 2	Visit 2.1	Visit 3	Visit 4	Visit 5	Visit 6
	Screening and enrollment	Start of treatment					End of treatment
	−60/−30 d	Day 0 (Wk 0)	Wk 4 ± 3 d after visit 2	Wk 13 ± 1 wk after visit 2	Wk 26 ± 1 wk after visit 2	Wk 39 ± 1 wk after visit 2	Wk 52 ± 2 wks after visit 2
**Inclusion/exclusion criteria**	✓	✓					
**Written informed consent**	✓						
**Demographic data***	✓						
**Vital signs (BP, HR, T, RR) and body weight**	✓	✓	✓	✓	✓	✓	✓
**Physical examination**	✓	✓	✓	✓	✓	✓	✓
**Neurological examination** ‡	✓	✓	✓	✓	✓	✓	✓
**Neuropsychological assessment** §	✓				✓		✓
**General blood tests** ‖	✓			✓	✓	✓	✓
**Biomarkers:** **24-OH-cholesterol**	✓			✓	✓	✓	✓
**Biomarkers:** **Oxysterols** **Lyso-sm-509**	✓				✓		✓
**EKG**	✓			✓	✓	✓	✓
**Medication dispensing**		✓		✓	✓	✓	✓
**Brain MRI**	✓						✓
**Brain ^18^FDG-PET scan**	✓				✓		✓
**Oculography**	✓				✓		✓
**Abdominal ultrasound**	✓				✓		✓
**Lumbar puncture**		✓†					✓†
**AE recording**	✓	✓	✓	✓	✓	✓	✓
**Concomitant medication recording**	✓	✓	✓	✓	✓	✓	✓
**Patient’s journal**		✓		✓	✓	✓	✓
**Pregnancy test**	✓	✓		✓	✓	✓	✓

AE = adverse event, BP = blood pressure, EKG = electrocardiogram, HR = heart rate, MRI = magnetic resonance imaging, RR = respiratory rate, T = temperature.

(1) Includes genetic diagnosis.

‡ Includes Ataxia Scale (SARA), Dysphagia Scale (EAT-10), Pineda Disability Scale.

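### The 52-week change in plasma 24-OH-cholesterol mixes 25 mg/d with higher doses triggered by that same marker, so it cannot show engagement at 25 mg/d; the scheduled week-13 sample can

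*Protocol article*

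**What the plan says.** **Dose.** Section 2.3 states "All patients will be treated orally with 25 mg/d of EFV for 52 weeks (1 year), in addition to SoC". It then makes an exception: "those patients with no evidence of a blood 24-OH-Cholesterol increase ≥ 1.5 times their baseline levels will have their EFV dose increased". The ceiling given there is 200 mg/d. Section 2.3.1 gives the same threshold but a softer action: "we shall consider increasing the dose to up to 200 mg/d". The Abstract, section 1.2 and section 1.4 describe only the fixed 25 mg/d for 52 weeks, and the primary objective in Table 1 (section 1.3) names 25 mg/d.

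**Why 25 mg/d.** Section 2.3.1 explains the choice as "considering that the desired effect should be observed with this dose". It uses the rise in plasma 24-OH-cholesterol to decide whether that expectation has been met.

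**Monitoring.** "we will perform successive blood tests (every 3 months", according to section 2.3.1. Table 3 (section 2.7.1) has 24-OH-cholesterol at Visit 1 (30 to 60 days before treatment starts) and at weeks 13, 26, 39 and 52. There is none at week 0 or week 4, so the first on-treatment sample is the one at "Wk 13 ± 1 wk after visit 2".

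**Outcome and analysis.** Table 2 (section 2.7) lists "Plasma 24-OH-Cholesterol level" among the biological outcomes, and that row gives no time point. Section 2.14 applies the primary outcome's technique to the secondary outcomes. That technique is an ANCOVA whose dependent variable is measured at 52 weeks; its covariates are study group and baseline CDR-SoB. It has no term for dose received or for escalation.

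**The concern.** The marker does two jobs. It decides who gets more drug, and it is reported as a result. Patients whose marker does not respond at 25 mg/d are exactly those moved to a higher dose. By week 52 their values reflect that higher dose, but nothing in the outcome definition or the analysis separates them from patients still on 25 mg/d.

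At stake is the justification for the dose. The objective and the rationale both rest on 25 mg/d activating the enzyme. A raised week-52 level would naturally be read as confirming this, although most or all of the rise could come from doses of up to 200 mg/d, eight times the starting dose.

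**Working it through.** **Figures in the plan.** The plan gives no expected change, variance or power for this marker, and section 2.8 states that no formal sample size calculation was made for the 14 patients. The one arithmetic figure in the dose rationale checks: 600/25 = 24. The largest permitted increase is 200/25 = 8-fold.

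**Inputs from the protocol.** One baseline sample; on-treatment samples at weeks 13, 26, 39 and 52; threshold 1.5 times baseline (read as observed level ÷ baseline level ≥ 1.5); a single arm of 14.

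**Assumptions not in the documents.** Log-normal values; within-patient CV of 15% to 35% (10% to 40% in the trial-level check); the true ratios at each dose; the rule applied at weeks 13, 26 and 39 to every patient below threshold, with the new dose in force by the next visit.

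**Step 1: chance of passing the threshold with no effect.** The log-scale SD is s = √ln(1 + CV²). A ratio of two samples has SD s√2, so P(pass at one visit) = 1 − Φ(ln 1.5 / (s√2)).

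- CV 15%: s = 0.149, z = 0.405/0.211 = 1.92, P = 2.7%
- CV 25%: s = 0.246, z = 0.405/0.348 = 1.16, P = 12.2%
- CV 35%: s = 0.340, z = 0.405/0.481 = 0.84, P = 20.0%

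A patient stays at 25 mg/d only by passing at all three visits. These events are correlated through the shared baseline, so the fraction was simulated (400,000 patients per scenario). If 25 mg/d is inert, 99.8%, 97.8% and 95.0% of patients have been escalated before week 52 at the three CVs.

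**Step 2: all-patient ratio at week 52.** If 25 mg/d has a true ratio of 1.0 and the raised dose a true ratio of H, noise averages out over all patients and the geometric mean ratio is H raised to the escalated fraction.

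| CV | Week 13 | Week 52, H = 2.0 | Week 52, H = 1.0 |
|---|---|---|---|
| 15% | 1.00 | 2^0.998 = 2.00 | 1.00 |
| 25% | 1.00 | 2^0.978 = 1.97 | 1.00 |
| 35% | 1.00 | 2^0.950 = 1.93 | 1.00 |

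The simulated means agree.

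**Step 3: what a 14-patient trial would report.** A paired t-test on the log ratio stands in for the analysis, because the planned model has a group term but only one group. A positive result means two-sided p < 0.05 in the upward direction (nominal rate 2.5%). There were 20,000 trials per scenario, with CV 10% to 40% and 25 mg/d inert throughout.

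| True ratio at raised dose | Week 52 positive |
|---|---|
| 1.0 | 2.4% to 2.5% |
| 1.1 | 9% to 64% |
| 1.25 | 28% to 100% |
| 1.5 | 71% to 100% |
| 2.0 | 99% to 100% |

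Week 13 is positive in 2.3% to 2.6% of trials in every scenario, whatever the raised dose does.

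**Step 4: splitting later values by dose received.** Patients remain at 25 mg/d because their observed ratios were high, partly through a baseline that happened to read low. With a true ratio of 1.2 to 1.4 at 25 mg/d, 3% to 20% of patients are never escalated (0.4 to 2.8 of 14), yet their week-52 ratio averages 1.59 to 2.06. With no effect at any dose the group is only 0.2% to 5% of patients, that is, 14 × 0.002 = 0.03 to 14 × 0.05 = 0.7 patients.

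**The case against.** **The reading is not circular, and week 52 need not look positive.** A reader might infer that steering the dose by the marker makes the week-52 result favourable whatever the drug does. The documents do not support that. Escalation changes the dose, not the measurement. If efavirenz does nothing at any dose, the all-patient week-52 ratio stays at 1.00 and the error rate stays nominal. A rise would be real engagement by the titrated regimen. This stands, and it limits the point to attribution to a dose.

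**It is not shown to be the only engagement readout.** Table 2 also lists plasma oxysterols, and no section names a sole marker. This stands. It remains true that the dose rationale relies on 24-OH-cholesterol alone.

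**The time point may be settled elsewhere.** The Table 2 row fixes none, Table 3 has four on-treatment samples, and a statistical analysis plan that is not shown may choose among them. This stands in part. What is written links secondary outcomes to the 52-week technique without a dose term, and that combination cannot inform on 25 mg/d.

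**The rule may be discretionary.** Section 2.3.1 says only that an increase will be considered. If some low patients are not escalated, the dilution is smaller, so the figures above are an upper case.

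**A bias among never-escalated patients is largely hypothetical.** One might infer that they would appear as responders through selection alone. With no drug effect there would be fewer than one such patient expected among 14, and the protocol proposes no such split. This is therefore a caution for any later display, not a defect in a planned analysis.

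**The outcome is secondary and called exploratory.** That limits the consequence, but the correction is nearly free.

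**Conclusion.** The concern holds as a problem of attribution. Followed as written, the 52-week change in 24-OH-cholesterol describes a mixture of 25 mg/d and escalated doses, and the mixture is determined by the marker itself. It can support engagement by the titrated regimen; it cannot support engagement at 25 mg/d. With 25 mg/d inert and the raised dose doubling the level, the expected ratio is 1.93 to 2.00 at week 52 against 1.00 at week 13. With the drug inert at every dose, both are 1.00.

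These sizes rest on the assumed CVs, on the assumed effect of the raised dose, and on applying the rule to every patient below threshold. The qualitative conclusion needs only that some patients are escalated and that the higher dose has some effect on the marker. It does not touch the primary cognitive outcome's definition. The change should be made, because the plan already collects the sample that answers the question.

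**What to change.** In sections 2.7 and 2.14:

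1. Name the change from baseline to the week-13 sample, in all patients and before any dose increase, as the 25 mg/d readout of plasma 24-OH-cholesterol.
2. Report the week-52 level separately, described as the level reached under biomarker-guided dosing.
3. If later values are shown by dose received, label them descriptive and not evidence of dose response, because the groups are selected on the marker.

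The sponsor should also reconcile the definite escalation wording in section 2.3 with the discretionary wording in section 2.3.1, and both with the fixed 25 mg/d for 52 weeks in the Abstract and sections 1.2 and 1.4. Which rule applies is for the sponsor to decide.

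The cost is wording only: no extra sample, and items 1 to 3 change no dose. The small downside is that the 25 mg/d result covers 13 weeks instead of 52 and may look less favourable.

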### 2.4. Criteria for discontinuing or modifying allocated interventions

As mentioned before, all enrolled patients will receive EFV + SoC. The EFV will be discontinued if the investigator deems that it poses an unacceptable risk to the patient; the patient withdraws his consent; there is a significant violation of the study protocol; there is a loss to follow-up; or in case a study participant becomes pregnant.

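### The objective and design name 25 mg/d for 52 weeks, but a 24-OH-cholesterol rule, binding in one section and optional in another, can raise the dose to as much as 200 mg/d

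*Protocol article*

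**What the plan says.** All references are to the protocol article.

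**Fixed dose.** Section 1.4 states: "All enrolled patients will be treated orally with 25 mg/d of EFV for 52 weeks (1 year), in addition to SoC". The Abstract (Methods) and section 1.2 say the same. The aim at the end of section 1.1 is to "evaluate the efficacy and safety of EFV at an oral dose of 25 mg/d in patients diagnosed with adult or late juvenile-onset NPC", and the primary objective in Table 1 (section 1.3) reads "To evaluate the efficacy* and safety of EFV at an oral dose of 25 mg/d, in addition to standard treatment".

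**Escalation, binding.** Section 2.3 repeats the 25 mg/d regimen. It then says that patients without a blood 24-OH-cholesterol rise to at least 1.5 times baseline "will have their EFV dose increased up to 200 mg/d".

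**Escalation, optional.** Section 2.3.1 gives the same 1.5-fold trigger, tested every 3 months, but concludes "we shall consider increasing the dose to up to 200 mg/d". It does not say whether that decision is made per patient or for the cohort.

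**Modification section.** The heading of section 2.4 covers discontinuing or modifying the intervention. Its rule begins "The EFV will be discontinued if the investigator deems that it poses an unacceptable risk to the patient" and goes on to other reasons for stopping. Escalation does not appear.

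**Measurement and analysis.** Table 3 schedules 24-OH-cholesterol at baseline and at weeks 13, 26, 39 and 52. The primary outcome is read at week 52 (section 2.7). The ANCOVA in section 2.14 has a study-group term and baseline CDR-SoB, with no term for dose or escalation.

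**The concern.** Two things are wrong as written.

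First, the sections give different instructions for the same patient. Under section 2.3, leaving a patient who misses the biomarker threshold on 25 mg/d is a deviation. Under section 2.3.1 it is not. Under the Abstract and sections 1.2 and 1.4 read literally, raising the dose is itself a departure from the design.

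Second, the objective is not worded for a regimen that can change. The trial has one arm and its primary outcome is read after three possible escalation points. Once a patient is escalated, that patient's week-52 cognitive outcome reflects a mixture of doses. The all-patient result then belongs to the strategy of starting at 25 mg/d and raising the dose if the biomarker does not respond. A report that follows the objective's wording would credit that result, benefit or harm, to 25 mg/d.

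**Working it through.** **Inputs.** Named dose 25 mg/d (sections 1.1, 1.3, 1.4). Ceiling 200 mg/d (sections 2.3, 2.3.1). Antiretroviral dose 600 mg/d (section 2.3.1). On-treatment 24-OH-cholesterol at weeks 13, 26, 39 and 52 (Table 3). Planned enrolment 14 (section 2.8). One arm (section 2.10). The document gives no expected escalation rate, so a range is assumed below.

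**1. The plan's own figure.** Section 2.3.1 puts the trial dose at 24 times below the antiretroviral dose. 600 / 25 = 24, so this is reproduced.

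**2. Possible dose range.** 200 / 25 = 8. The ceiling is 8 times the dose in the objective and one third of 600 mg/d (600 / 200 = 3).

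**3. Time above the named dose.** The week-52 test comes at the end of treatment, so the tests that can change exposure are those at weeks 13, 26 and 39. If the dose is raised on the day of the test in week w:

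- share of the year above 25 mg/d = (52 − w) / 52
- time-averaged dose, if raised straight to the ceiling = (25w + 200(52 − w)) / 52

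| Test week w | Weeks above 25 mg/d | Share of 52 weeks | Average daily dose at ceiling |
|---|---|---|---|
| 13 | 39 | 75% | (325 + 7,800) / 52 = 156.25 mg |
| 26 | 26 | 50% | (650 + 5,200) / 52 = 112.5 mg |
| 39 | 13 | 25% | (975 + 2,600) / 52 = 68.75 mg |

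These are upper limits. A delay in acting on the test, or a smaller increase, lowers them.

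**4. Chance that the result is affected.** Assume each of 14 patients escalates independently with probability q. Then P(at least one escalates) = 1 − (1 − q)^14, and the expected number left on 25 mg/d is 14(1 − q).

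| Assumed q | P(at least one) | Expected number left on 25 mg/d |
|---|---|---|
| 0 | 0% | 14 |
| 10% | 77% | 12.6 |
| 25% | 98% | 10.5 |
| 50% | >99.9% | 7 |

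Only with no escalation do the week-52 data describe 25 mg/d for 52 weeks in everyone.

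**5. Can a split by dose recover the 25 mg/d question?** Under section 2.3, patients still on 25 mg/d are those whose 24-OH-cholesterol reached the threshold. That biomarker tracks the enzyme activation through which the drug is meant to work. The unescalated subset is therefore selected on early response, and comparing it with the escalated subset confounds dose with response.

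**6. What remains clean.** Week 13 is the first on-treatment 24-OH-cholesterol measurement. No escalation triggered by this biomarker can precede it, so it is a 25 mg/d reading in every patient tested.

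**The case against.** The fairest defence is that section 2.3 states 25 mg/d and then its exception in the next sentence. The shorter statements elsewhere can then be read as summaries of the starting dose. Section 2.3.1 also expects the desired effect at 25 mg/d, so few or no patients may escalate. This has some force: the sharpest contradiction is between the binding and the optional wording, and the summaries are better called incomplete. It does not remove that contradiction, or the fact that the objective names one dose.

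Some stronger readings are tempting, and the document does not support them:

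- **That the trial cannot answer its objective.** This depends on how many patients escalate, which is unknown. With none, the objective is answered as worded.
- **That the analysis treats everyone as receiving 25 mg/d.** Section 2.14 lacks a dose term, but it does not label patients by dose. Tabulations by dose could sit in an analysis plan that is not shown, so their absence here is no fault in itself.
- **That a week-52 24-OH-cholesterol outcome is spoiled by titration.** Table 2 lists the plasma level without a time point, biological outcomes are called exploratory, and week 13 supplies an untitrated value. The caution applies only to values after escalation becomes possible.
- **That escalated patients say nothing about 25 mg/d.** Their safety and biomarker data before the change still do. The separate safety row in Table 1 names no dose; only the primary objective ties safety to 25 mg/d.

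The limits of a small uncontrolled trial are conceded in the Discussion, but titration is not among them.

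**Conclusion.** The point stands in conditional form. The article contradicts itself on whether escalation is required, optional or absent, and its primary objective names a single dose that its own rule may change. If any patient is escalated, the all-patient week-52 result estimates a biomarker-guided 25 to 200 mg/d strategy, and a split by dose received cannot recover the 25 mg/d effect without selection.

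The size is bounded rather than known: at most 8 times the named dose, and at most 75% of the year above it for one patient. Those limits assume same-day action at week 13 and, for the 8-fold figure, an increase to the ceiling. The chance that at least one of 14 patients is escalated is 77% at an assumed 10% per-patient rate and 98% at 25%, assuming independence. The text should be corrected, because it concerns the intervention itself and what the primary result means.

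**What to change.** 1. The sponsor must reconcile the Abstract and sections 1.1, 1.2, 1.3 (Table 1), 1.4, 2.3, 2.3.1 and 2.4 on whether escalation is fixed, discretionary or absent. Which of these is right, and at what dose, is a clinical decision and is not proposed here.
2. If any escalation remains, word the primary objective and the conclusion as the effect of the biomarker-guided regimen, with the all-patient result as its estimate.
3. List responder status by each patient's dose history, and adverse events by dose at onset. Present these descriptively, not as a comparison of doses.
4. Use the week-13 24-OH-cholesterol value as the readout for 25 mg/d in all patients tested, and report later values as values under titration. The last value before escalation would be a poor substitute: in escalated patients it is by construction a value that missed the threshold, it falls at different weeks, and unescalated patients have none.

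The cost is protocol wording and an extra table; the week-13 sample is already scheduled. The downside is that the claim about 25 mg/d becomes narrower.
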